### Interim analyses {21b}

None planned. There are no anticipated problems that are detrimental to the participant.

### Methods for additional analyses (e.g., subgroup analyses) {20b}

None planned.

### Methods in analysis to handle protocol non-adherence and any statistical methods to handle missing data {20c}

The intention-to-treat principle (ITT) will be used to analyze the data.

### Plans to give access to the full protocol, participant-level data, and statistical code {31c}

The plans of this protocol are available on the clinical trial registration website (https://www.chictr.org.cn).

## Oversight and monitoring

### Composition of the coordinating center and trial steering committee {5d}

The principal investigators (PIs) of this clinical trial are PI # 1, [name], at the Shanghai Seventh People’s Hospital, Shanghai University of Traditional Chinese Medicine, and PI # 2, [name], at the Shanghai Seventh People’s Hospital, Shanghai University of Traditional Chinese Medicine. PI # 1 designs the concept of the research project including the stimulation protocol, the SSRT design, and all the neurophysiological recording methods. PI #1 also performs and analyzes along with her research team all neurophysiological recordings for all study participants of the clinical trial. PI # 2 leads the implementation of multi-target transcranial alternative current stimulation and regular rehabilitation training as well as the clinical assessments for study participants at the hospital. The trial steering committee is composed of the PIs and dedicated research staff.

The PIs and dedicated research staff will form the trial steering committee, which is accountable for coordinating and managing the whole project. Study governance for this single-site study is organized into the oversight team, recruitment team, intervention deployment and assessment team, neurophysiological recording and neuroimaging team, blood sample team, data management, and analysis team. The oversight team is led by the PIs and is responsible for global oversight of the conduct and progress of the study. Each team is led by a dedicated research staff or clinician. Each team works with the oversight team to develop and monitor standard operating procedures. Each team has a weekly meeting with the PI focused on decisions and progress within their scope of responsibility. Full study meetings are held quarterly and as needed.

### Composition of the data monitoring committee, its role, and reporting structure {21a}

Not applicable. As tACS technique is a low-risk intervention which has no substantial safety issues, there will not be a data monitoring committee.

### Adverse event reporting and harms {22}

Due to the tACS technique being a low-risk intervention, no adverse event reporting is anticipated. During the tACS intervention, a professional doctor will always accompany the entire process. If the participant experiences any discomfort, the intervention will be stopped and proper treatment will be provided by the professional.

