### Interventions

#### Explanation for the choice of comparators {6b}

The study included one sham and two active stimulation interventions delivered to three parallel groups.

In the SS group, a “pseudo stimulus” button will be discreetly activated, providing a semblance of stimulation to the subject without their awareness. For the ST group, the current channel will solely target M1, while the remaining three brain areas will receive pseudo stimulation, akin to the SS group. In the MT group, all four channels will be activated simultaneously. The entire process of electrical stimulation intervention will be closely supervised by a proficient clinical operator in conjunction with emergency personnel. Sham stimulation enables a placebo comparator to the active conditions.

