#### Provisions for post-trial care {30}

There is no anticipated harm for tACS intervention. However, participants who feel uncomfortable, such as skin itching, will be evaluated by the neurologist for further necessary treatment.

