### Outcomes {12}

Assessments will be conducted by physiotherapists blinded to the group allocation at various designated time points, as outlined in Table 1. Additionally, a comprehensive questionnaire (administered during week 0) will capture baseline information, including age, gender, symptoms, disease severity, duration, prior treatment, and medication history, which will be recorded using a questionnaire. Additionally, any encountered side effects throughout the course of the study will be promptly documented and reported in real time.

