## Assignment of interventions: blinding

### Who will be blinded {17a}

It should be noted that complete blinding of both researchers and participants to the allocation of intervention targets is not feasible due to the inherent visibility of stimulation targets. Therefore, blinding will be selectively implemented, extending exclusively to the assessors and statisticians responsible for data collection and final statistical analyses.

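### The harms section {22} expects no adverse event reporting and gives no recording step, which conflicts with the duty in Outcomes {12} to record and report every side effect

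*Protocol article*

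**What the plan says.** Three sections of the protocol article deal with side effects.

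- **Adverse event reporting and harms {22}:** because tACS is regarded as low risk, "no adverse event reporting is anticipated". A doctor is to be present throughout stimulation. The section continues: "If the participant experiences any discomfort, the intervention will be stopped", with treatment to follow. It mentions no form, log or recipient for a report.
- **Outcomes {12}:** "any encountered side effects throughout the course of the study will be promptly documented and reported in real time". The sentence sets no threshold and makes no exception for mild or expected effects.
- **Provisions for post-trial care {30}:** it states that no harm is expected, and then that "participants who feel uncomfortable, such as skin itching, will be evaluated by the neurologist".

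Two design features bear on how side effects would be noted. Under the choice of comparators {6b}, the sham arm gets no active stimulation and the single-target arm gets M1 only. For the third arm, "In the MT group, all four channels will be activated simultaneously". Under Who will be blinded {17a}, "complete blinding of both researchers and participants to the allocation of intervention targets is not feasible".

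**The concern.** Section {22} is where a physiotherapist, nurse or doctor would turn to learn what to do with an adverse event. It tells them that reporting is not expected and that discomfort calls for stopping and treating. The instruction to record and report stands elsewhere, at the end of the opening paragraph of the outcomes section, and {22} neither repeats it nor refers to it. Someone who works from {22} alone could treat itching under an electrode, end the session and leave no record, and would not have contradicted that section.

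What is at stake is the completeness and evenness of the safety data. The arms differ in how much current is delivered, and the people running sessions cannot be fully blinded to the targets. If side effects are noted only when someone happens to mention or notice them, the threshold for noting them could differ by arm. The trial's Discussion already calls the multi-target method well tolerated, so readers will look for safety data behind that description.

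**Working it through.** There is no plan figure to reproduce and no sample size, power or alpha calculation that bears on the point. The check is a comparison of the sections.

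1. **Is an event expected?** {22} and {30} both lean on low expected risk. Yet {30} names skin itching and assigns a neurologist to assess it, and {22} lays down what happens if there is discomfort. The protocol therefore allows for events.
2. **Must an event be recorded?** {12}: yes, any side effect, promptly. {22}: no recording step at all.
3. **Must an event be reported?** {12}: yes, as it occurs. {22}: "no adverse event reporting is anticipated". The clause is about reporting, not about how often events happen. It cannot be fully squared with {12} once step 1 is granted: if itching is foreseen, and any side effect is to be reported, then some reporting should be anticipated.
4. **Does {22} cancel {12}?** No. It states an expectation. It does not forbid reporting or say that {12} is displaced. The duty in {12} survives, but the protocol gives staff two different signals.
5. **Could recording differ by arm?** {6b} gives no active channel in the sham arm, one in the single-target arm and four in the multi-target arm. {17a} limits blinding to assessors and statisticians. {12} opens with blinded assessors but does not say who records side effects, and {22} places a doctor at the session. An uneven threshold is therefore possible. The article does not establish that it would occur.
6. **Does it touch efficacy?** No. The SRTT and EEG outcomes and their analysis do not depend on how side effects are recorded.

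**The case against.** The strongest reply is that the duty already exists. {12} is unconditional, and the clause in {22} is a forecast. The article uses the same idiom elsewhere: the sections on discontinuing interventions {11b} and on interim analyses {21b} both say that no problems are anticipated. {22} then provides for discomfort, so it does not assume that nothing will happen. On this view the defect is one of placement and wording. That much stands, and it is why the point is minor. It does not remove the conflict, because the section devoted to harms should carry the duty and not point away from it.

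The reply can go further. An article need not describe how side effects are elicited, and standard operating procedures may cover it. No comparison of tolerability between arms is among the stated objectives or outcomes. Both statements are correct. The lack of an elicitation method is therefore not counted as an error here; the common question proposed below is an inexpensive improvement made while {22} is being corrected.

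A reader might infer three stronger things that the documents do not support:

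- **That the trial will not collect harms, or will under-record them.** {12} commits to recording any side effect, and nothing shows that staff would ignore it.
- **That the lack of a data monitoring committee makes the gap worse.** The article does say that "there will not be a data monitoring committee", but such a committee ordinarily reviews events already recorded. Its absence says little about whether they are recorded.
- **That the shortfall can be put into figures.** The article gives neither a side-effect rate nor a share likely to be missed. Any calculation would have to assume the under-recording that is in question.

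**Conclusion.** The concern holds as an inconsistency of text. {22} expects no reporting and gives no recording step, {12} requires both, and {30} names a side effect that would have to be reported. Under-recording, or recording that differs by arm, is a possible consequence that the documents do not show. No numerical size can be attached. The severity is minor: the primary efficacy analysis is untouched, the {12} duty remains in force, and the doctor's presence at sessions is not in question. The conclusion rests on reading the sections as they stand in the article; a fuller protocol or operating procedure may already hold a recording step, but the clause in {22} would still need to be brought into line with {12}.

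**What to change.** 1. Delete the clause in {22} stating that no reporting is anticipated.
2. Have {22} restate the {12} duty, so that every side effect, including an expected one such as skin itching, is recorded promptly and reported.
3. Ask every participant the same side-effect question, in the same words, at each session in all three arms. Staff already present can do this. A fixed question is less open to differences in threshold between arms than noting whatever comes up, which matters when those staff cannot be fully blinded.
4. Report side effects and stimulation stops by arm.

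The cost is a wording change, a short checklist at each session and one extra table. If daily means all 14 days of the two weeks, the checklist comes to at most 39 × 14 = 546 brief entries over the whole trial. Neither the sample size nor the analysis of any efficacy outcome changes.

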### Frequency and plans for auditing trial conduct {23}

The Ethics Committee will provide ongoing regulatory monitoring. Planned site visits or the trial dataset exploration will occur, and the trial steering committee and Ethics Committee will meet annually to review the trial conduct upon study initiation yearly.

### Plans for communicating important protocol amendments to relevant parties (e.g., trial participants, ethical committees) {25}

The Ethics Committee of the Shanghai Seventh People’s Hospital needs to review and approve any significant changes to the protocol or informed consent which might cause participant safety risks or impact the scientific soundness of the project.

## Dissemination plans {31a}

We will disseminate the study’s results widely through conference presentations or publications. Publications in high-impact, open-access medical journals and talks at national and international medical conferences will serve this purpose.

## Discussion

The tACS technique has gained increasing attention due to its potential to modulate endogenous neural oscillations through weak electrical currents [42]. The 40-Hz multi-target tACS protocol, grounded in intrinsic brain oscillatory activities, presents a promising and well-tolerated treatment for improving motor learning in stroke patients. The acquisition of novel motor skills, a cornerstone of human behavior, underscores the significance of motor learning [43]. Numerous research articles have confirmed the beneficial impact of tACS, particularly 40 Hz tACS, in exploring memory [44], learning [45], and higher cognitive function [11, 46], all of which are pivotal for effective motor learning. Despite these findings, the impact of 40 Hz tACS on the motor learning of stroke patients is still unclear.

In light of this, we devised three groups—the SS group, the ST group, and the MT group—to explore the therapeutic potential of 40 Hz tACS in stroke patients. This study also seeks to ascertain whether variations in stimulation targets yield divergent treatment outcomes among the three groups. Importantly, we will elucidate the brain mechanism and physiological underpinnings that drive the therapeutic effects through EEG, TMS, MRI, and blood RNA sequencing. In addition, we will assess the improvement in upper limb function in stroke patients using the BBT before and after the 2-week intervention. If 40 Hz tACS proves efficacious, it could become a valuable treatment option for enhancing motor learning in stroke patients.

Nonetheless, it is important to acknowledge certain limitations within the protocol. First, the duration of tACS intervention may not be optimized, and determining the most effective intervention duration remains uncertain. Second, the potential influence of patient-specific characteristics, such as stroke type and location, on treatment outcomes remains unclear. To address these limitations, we intend to conduct further research to refine and optimize the protocol’s outcomes in the future.

## Trial status

Participant recruitment will start in February 2024 and is expected to be completed at the end of April 2024. The version of this protocol is the 2nd version.

## Abbreviations

tACS: Transcranial alternating current stimulation
TMS: Transcranial magnetic stimulation
MRI: Magnetic resonance imaging
SRTT: Series reaction time test
EEG: Electroencephalogram
MEP: Motor evoked potential
CMCT: Central motor conduction time
SICI: Short interval intracortical inhibition
ICF: Intracortical facilitation
BBT: Box and Block test
NIBS: Noninvasive brain stimulation
M1: Primary motor cortex
S1: Primary sensory cortex
DLPFC: Dorsolateral prefrontal cortex
CB: Cerebellar
RT: Rest threshold
ISI: Interstimulus interval
NGF: Nerve growth factor
NAS: Numeric Analog Scales
ITT: Intention to treat
